### 2.3. Outcomes Measurement

The same outcomes will be included in both studies. All of them will be assessed by a trained physical therapist in all groups the previous week, the following week, and 15 days after the 10 intervention sessions. The procedure is presented in Figure 1.

Every outcome will be measured in the ON state of PD patients, 1 h after taking their dopaminergic medication, to ensure their comfort. Nevertheless, Kings Parkinson’s Disease Pain Scale (KPDPS), CPM and TS will be also measured in OFF state, 30 min before medication intake, to assess the effects of both neuromodulation therapies when dopaminergic medication is not acting.

#### 2.3.1. Main Outcomes

##### King’s Parkinson’s Disease Pain Scale (KPDPS)

The KPDPS is a PD specific scale that evaluates the localization, frequency, and intensity of pain. It contains 14 items distributed in 7 domains: 1. Musculoskeletal Pain; 2. Chronic Pain; 3. Fluctuation-related Pain; 4. Nocturnal Pain; 5. Oro-facial Pain; 6. Discoloration, Oedema/Swelling Pain; 7. Radicular Pain. Each item is scored by severity (0, none to 3, very severe) multiplied by frequency (0, never to 4, all the time) resulting in a subscore of 0 to 12, the sum of which gives the total score with a theoretical range from 0 to 168. The KPDPS is considered a valid and reliable scale, with a Chronbach’s Alpha = 0.99 [52]. In addition, it is the unique validated scale in the assessment of pain in PD patients [53].

##### Brief Pain Inventory (BPI)

The BPI-short form will be used. It contains 15 items, including 2 multi-item scales to measure the intensity of pain and its impact on the function and welfare of patients. It also presents open questions to assess the localization of pain and the treatment used for its management, just as its effectiveness. The BPI is a valid and reliable scale, considered precise for the evaluation of severity of pain, easy to administer and interpret and applicable to diverse pain etiologies [54]. Its short form has been considered “recommended with caution” for the assessment of pain in PD patients, fulfilling every required criteria [53].

##### Pain Pressure Threshold (PPT)

PPT will be assessed with a handheld pressure algometer (FPX Model, Wagner Instruments, Greenwich, CT, USA). Two PPTs will be measured, one over the most painful area (peripheric hyperalgesia) and the other one over the middle of the distal phalanx of the thumb (central hyperalgesia). The PPT will be applied with the algometer perpendicular to the skin increasing at a rate of 1 kg/s [34] until the first sensation of pain. 3 measures with 30-s rest between them will be performed, taking the average as PPT. The algometry reliability to assess the PPT have demonstrated to be good-excellent, with an intraclass correlation coefficient of 0.84–0.96 [55].

##### Temporal Summation (TS)

The TS phenomenon, which represents excitatory modulation processes, will be generated through the application of 10 pulses of the handheld pressure algometer over the middle of the distal phalanx of the thumb with the intensity of the PPT, previously calculated [56]. In each pulse, pressure intensity will be increasing at a rate of 2 kg/s over the previously determined PPT intensity, leaving an interstimulus interval of one second according to the optimal method reported for inducing TS with pressure pain [57]. Before the first pressure pulse, subjects were taught to use a verbal numeric pain rating scale (VNPRS) to rate the pain intensity of the 1st, 5th, and 10th pressure pulses. The VNPRS ranges from 0 (“no pain”) to 10 (“the worst possible pain”) [58].

##### Conditioned Pain Modulation (CPM)

The CPM task, which assess the descending pain modulatory system, will be separated 5 min from TS task to prevent contamination. The PPT will be assessed in the middle of the distal phalanx of the thumb with the previously mentioned handheld algometer, corresponding to the first test stimulus. Afterwards, the patient will immerse the contrary hand up to the wrist into stirred ice-cold water (0–4 °C) maintaining it for 3 min, corresponding to the conditioning stimulus. If the pain is unbearable before the 3 min, the patient will be able to remove his/her hand. Immediately after removing the hand, a second PPT measure will be performed in the same place as the first one, corresponding to the second test stimulus [59]. After 1-min rest, a third PPT will be measured to assess the CPM residual functioning. The combination of PPT induced by handheld pressure algometer as test stimulus and cold water as conditioning stimulus are considered to be the most reliable method to assess CPM [60].

#### 2.3.2. Secondary Outcomes

##### Psychological and Functional Outcomes

The emotional outcomes assessed will be depressive symptoms, measured by Beck Depression Inventory (BDI), anxiety, measured by Stait-Trait Anxiety Inventory (STAI) and fear of movement-related pain, measured by Tampa Scale of Kinesiophobia (TSK-11). Cognitive outcome assessed will be catastrophizing thinking, measured by Pain Catastrophizing Scale. Finally, the functional outcome assessed will be the Unified Parkinson’s Disease Rating Scale (UPDRS), the most used scale for the assessment of disability in PD patients.

##### Neuropsychological Outcome

Reaction Times (RT) task will be performed through 2 related subtasks using a 15-inch monitor, controlled by Presentation^®^ software (http://www.neurobs.com).

The first subtask will be the Finger Taping (FT) task, to measure motor function [61]. This task is very sensitive to the slowing down of responses [62] and it has been also used as a measure of motor speed in PD patients [63]. In this task, following the Strauss application norms [62], the participants will be instructed to press the spacebar on the keyboard as fast as possible and repeatedly with the index finger. Five 10 s attempts will be performed with the dominant hand. The average time between two consecutive taps in the five trials will be the dependent variable.

Following this, the Simple Reaction Time (SRT) task will be performed to measure simple perception and sustained alertness [64]. Participants will be instructed to press the left mouse button as fast as possible when the stimulus “+” appears in the center of the screen at a size of 2 cm × 2 cm. The order of appearance will be constant for all participants. The task will consist of 50 trials lasting 2–3 min [65].

##### Neurophysiological Outcomes

The excitability of pain-related pathways will be measured by Transcranial Magnetic Stimulation (TMS) markers. Firstly, single pulse TMS will be performed to acquire resting motor threshold (rMT), motor evoked potentials (MEPs) and cortical silent period (CSP). Magstim Rapid2 device with a figure-of-eight magnetic stimulator coil will be used. For all assessments, the magnetic stimulator coil will be placed firstly on the right and secondly on the left M1 with a 5 min rest interval, and surface electromyogram from the contralateral first dorsal interosseous muscle will be recorded. TMS used amplitudes and EMG recordings will be recorded and stored in a computer for off-line analysis [66]. Stimulation output used to reach the rMT, MEP amplitudes and silent periods duration will be taken as outcomes.

Brain activity will be measured by Electroencephalography (EEG). An actiCHamp amplifier (Brain Vision LLC, Morrisville, NC, USA) will be used to amplify and digitize the EEG data at a sampling frequency of 512 Hz. The EEG data will be stored in a PC running Windows 7 (Microsoft Corporation, Washington, DC, USA). EEG activity will be recorded from 64 positions with active Ag/AgCl scalp electrodes (actiCAP electrodes, Brain Vision LLC, Morrisville, NC, USA). The ground and reference electrodes will be placed on AFz and on FCz, respectively Electroencephalography acquisition will be carried out by NeuroRT Studio software (Mensia Technologies SA, Paris, France). The EEG signal processing procedure will be performed using MATLAB functions (MathWorks Inc., Natick, MA, USA), specifically the EEGLab toolbox. The EEG registers performed will be resting (1 min), while FT task (30 s each hand, beginning with the dominant one), while wrist-extension task (5 min each hand, beginning with the dominant one) and with eyes closed (5 min). The participants will be asked to relax in the resting condition; the investigator will ensure they do not fall asleep, especially in resting and in eyes closed registers. Spectral entropy correlation, coherence and interhemispheric divergence differences among experimental group and controls will be analyzed as outcomes.

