#### 2.1.2. AO+MI-Based Study

This study will be a double-blinded experimental longitudinal prospective randomized controlled trial with a parallel design. The randomization will be realized through the GraphPad software (GraphPad Software, Inc CA 92037 EE.UU.). All the participants who fulfil the inclusion criteria and have none of the exclusion one will be randomly allocated in two groups: AO+MI through a Brain-Computer Interface (BCI) training paradigm in Virtual Reality (VR) (or neurogame) (AO+MI-BCI) or AO of non-related with movement illustrations (AO-control). Allocation concealment will be ensured by the inclusion of the assigned group in closed opaque envelopes that will be opened at the time of the intervention. Double-blind criteria will be achieved by following the same protocol with the same instruments in both groups. The evaluator will not be able to stay in the same room during the intervention and patients will not know the instructions and specific hypothesis of each protocol. The statistician will be blinded through the assignment of neutral numbers to both groups. Patients recruited will not meet in waiting rooms to avoid them to comment on their experience during the protocol. Unblinding will be permissible when any event could suppose a risk for the patient’s health. The Institutional Research Committee and Institutional Ethics Committee of Hospital Universitario 12 de Octubre approved this study with code 20-514 on December 2020 and the trial was registered in Clinical Trial, NCT04651478.

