## Figures and Tables

**Figure 1 brainsci-11-00065-f001:**
[figure not shown]
Schematic representation of both tDCS-based study and AO+MI-based study experimental procedures. It includes the days of the week and duration of each block of outcomes measurement in pre- and post-evaluation (KPDPS, King’s Parkinson’s Disease Pain Scale; BPI, Brief Pain Inventory; CPM, Conditioned Pain Modulation; TS, Temporal Summation; PPT, Pain Pressure Threshold; Psychological measures: Thursday/60–90 min; and Neuropsychological, Functional, Neurophysiological measures: Friday/120 min) and each treatment option (Experimental or Control group: Monday to Friday/10 sessions with the duration of each specific protocol, described in intervention protocols).

**Table 1 brainsci-11-00065-t001:** Additional inclusion and exclusion criteria for the transcranial direct current stimulation (tDCS)-based Study.

Inclusion Criteria	Exclusion Criteria
Older than 18. Neuroimaging study without previous pathologies. Score > 5 in transfers (bed to chair and back) item in Barthel Index. Score = or > 24 in Mini-Mental State Examination. Tolerability for the application of electrotherapy. Able to provide informed consent to participate in the study.	History of neurologic disease different from PD. Presence of non-related to PD pain. Dermatologic problems, wounds, or ulcers in the electrode’s application area. Presence of implants or metal pieces in the head. Presence of cardiac pacemaker, vagal, brain or transcutaneous stimulators, medication pumps, ventriculoperitoneal shunts or aneurysm clips. Significative difficulties in language. History of alcohol or drugs abuse. Non-controlled medical problems. Pregnancy. Epilepsy.

PD, Parkinson’s Disease.

**Table 2 brainsci-11-00065-t002:** Additional inclusion and exclusion criteria for AO+MI-based study.

Inclusion Criteria	Exclusion Criteria
Older than 18. Neuroimaging study without previous pathologies. Score > 5 in transfers (bed to chair and back) item in Barthel Index. Score = or > 24 in Mini-Mental State Examination. Able to provide informed consent to participate in the study.	History of neurologic disease different from PD. Presence of non-related to PD pain. Dermatologic problems, wounds, or ulcers in the electrode’s application area. Significative difficulties in language. History of alcohol or drugs abuse. Non-controlled medical problems. Pregnancy.

PD, Parkinson’s Disease.

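### The AO+MI trial schedules TMS over both motor cortices, but its exclusion list omits the head-metal, implanted-device and epilepsy items that the tDCS trial applies

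*Protocol article*

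**What the plan says.** Section 2.3 (Outcomes Measurement) makes the outcome set common to the two trials: "The same outcomes will be included in both studies". It also fixes who is measured and when: "All of them will be assessed by a trained physical therapist in all groups the previous week, the following week, and 15 days after" the ten intervention sessions.

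Section 2.3.2, under Neurophysiological Outcomes, makes TMS one of those outcomes: "Firstly, single pulse TMS will be performed to acquire resting motor threshold (rMT), motor evoked potentials (MEPs) and cortical silent period (CSP"). It is done on both sides of the head: "the magnetic stimulator coil will be placed firstly on the right and secondly on the left M1 with a 5 min rest interval". The caption of Figure 1, which lists the neurophysiological measures, covers both trials: "Schematic representation of both tDCS-based study and AO+MI-based study experimental procedures".

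Eligibility is set trial by trial. Section 2.1 refers the reader to Tables 1 and 2 for the criteria it does not give itself. Table 1, for the tDCS trial, excludes among others "Presence of implants or metal pieces in the head. Presence of cardiac pacemaker, vagal, brain or transcutaneous stimulators", and goes on to pumps, shunts, aneurysm clips and, as a separate item, epilepsy. Table 2, for the AO+MI trial, goes from skin problems at the electrode site to the end of its list without any of these: "application area. Significative difficulties in language. History of alcohol or drugs abuse. Non-controlled medical problems. Pregnancy". Section 2.1.2 then randomises on the listed criteria alone: "All the participants who fulfil the inclusion criteria and have none of the exclusion one will be randomly allocated in two groups".

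**The concern.** The AO+MI intervention is EEG, imagery and virtual reality, with no current or magnetic field applied to the head. A shorter exclusion list would suit that intervention. The assessments are another matter: AO+MI patients get the same TMS measurements as tDCS patients. Table 2 appears to have been fitted to the intervention, with the shared TMS outcome overlooked.

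At stake is the safety of device carriers. Brain stimulators and medication pumps are plausible in patients recruited from a Parkinson's clinic, and pacemakers are plausible in older patients generally. The sponsor keeps all of them out of one trial of transcranial stimulation, yet the companion trial admits them and schedules magnetic pulses over both motor cortices. There is a smaller analytic consequence. If staff quietly skip TMS in such patients, values go missing under a rule the article does not state, in the MEP analyses and in the regression that uses resting motor threshold (section 2.5).

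**Working it through.** This is a comparison of stated criteria; the only arithmetic is counting.

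**Step 1. Does TMS apply to the AO+MI trial?** Section 2.3 shares all outcomes and assesses all groups. Section 2.3.2 does not limit TMS to one trial. The Figure 1 caption covers both. So it does.

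**Step 2. Compare the exclusion lists item by item (paraphrased).**

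| Exclusion | Table 1 (tDCS) | Table 2 (AO+MI) |
|---|---|---|
| Another neurologic disease | yes | yes |
| Pain unrelated to PD | yes | yes |
| Skin lesions at electrode site | yes | yes |
| Head implants or metal | yes | **no** |
| Pacemaker, stimulators, pumps, shunts, clips | yes | **no** |
| Language difficulties | yes | yes |
| Alcohol or drug abuse | yes | yes |
| Uncontrolled medical problems | yes | yes |
| Pregnancy | yes | yes |
| Epilepsy | yes | **no** |
| **Count** | **10** | **7** |

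Difference: 10 − 7 = 3 items.

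**Step 3. Does anything else in the AO+MI criteria close the gap?**

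- *Epilepsy.* The exclusion for another neurologic disease would normally catch it. In effect covered.
- *Shunts and aneurysm clips.* The neuroimaging inclusion criterion and the neurologic-history exclusion would probably remove some of these patients. Partly covered.
- *Medication pumps.* Section 2.3 times ON assessments at 1 h after a dose and OFF assessments at 30 min before one. Continuous dopaminergic infusion fits this poorly, but it is not excluded.
- *Cardiac pacemaker.* A stable pacemaker is not a neurologic disease, an imaging pathology or an uncontrolled medical problem. Not covered.
- *Brain stimulator for PD.* It treats PD itself, so the exclusion for other neurologic disease does not reach it. Not covered.
- *Head metal without brain pathology.* Not covered.

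**Step 4. Is there a TMS-specific screen or exemption?** None is stated. The safety procedures in section 2.2.1 concern tDCS sessions, and those in section 2.2.2 concern AO+MI training sessions. The TMS paragraph has neither a screen nor an exemption.

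**Step 5. Scheduled exposure per admitted carrier.** 3 visits (section 2.3) × 2 hemispheres (section 2.3.2) = 6 TMS hemisphere assessments. This is the schedule for every participant. The article gives no basis for estimating how many of the 32 planned AO+MI patients would be carriers, so no total is calculated.

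**The case against.** The strongest reply has three parts.

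*The real gap is narrower than three items.* Epilepsy is already caught, shunts and clips are largely caught, and pumps fit badly with the dose-timed visits. This is right as far as it goes: the count of three describes the printed lists, not the number of unprotected patient types. What remains is pacemakers, brain stimulators implanted for PD, head metal, and pumps in so far as the visit timing does not rule them out in practice.

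*The article never says these conditions contraindicate TMS.* Table 1 belongs to a trial delivering 2 mA for 20 min over ten sessions, and its electrotherapy-tolerability criterion is likewise absent from Table 2, so the extra items may be tDCS criteria only. Table 1 indeed gives no reasons, so the argument rests on reading across from one form of transcranial stimulation to another. But TMS is given in the tDCS trial too, and there these patients are excluded. The AO+MI trial has no stated protection for them whichever procedure prompted the exclusion.

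*A condensed article may leave a pre-procedure safety check to the full protocol.* A separate screen may well exist, and the article does not say TMS would proceed despite a contraindication. However, the article does not summarise eligibility in passing. It prints a criteria table for each trial, the two differ on exactly these items, and randomisation follows the table. That is an inconsistency in what is stated, not a detail left out for length.

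**Conclusion.** The concern holds. As written, a PD patient with a pacemaker, a brain stimulator, a medication pump or metal in the head can meet the AO+MI criteria, be randomised, and be scheduled for six TMS hemisphere assessments, although the companion trial excludes the same patient. The epilepsy item is missing from the list but is covered in practice.

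This should be fixed, as a safety correction to a secondary-outcome procedure. It does not touch the King's Parkinson's Disease Pain Scale outcome, the sample size or the main 2 × 3 ANOVA. The conclusion assumes that the printed tables are the operative criteria and that Table 1's reasons for excluding device and metal carriers from transcranial stimulation are relevant to TMS. An unpublished TMS screen would remove the practical risk but not the mismatch in the text.

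**What to change.** Preferred: copy the three items (head implants or metal, implanted devices, epilepsy) from Table 1 into Table 2. Adding epilepsy is mainly for consistency. The cost is a slightly narrower AO+MI population.

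Alternative, if device carriers are wanted in the AO+MI trial: add one sentence to the Neurophysiological Outcomes text saying that AO+MI patients with these contraindications do not undergo TMS and that their rMT, MEP and CSP values are missing by design. The cost is a few missing secondary values, under a rule fixed in advance.

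If a TMS safety screen already exists in the full protocol, state it in that paragraph and align Table 2 with it.

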### 2.4. Sample Size Calculation

#### 2.4.1. tDCS-Based Study

The simple size for the tDCS-based study was calculated using G*Power software (version 2.1, Heinrich-Heine-Universität Düsseldorf, Düsseldorf, Germany), taking into consideration the design of two intervention groups and three assessment times. The primary outcome was chosen to be King’s Parkinson’s Disease Pain Scale with an estimated effect size of F = 0.25. An α level of 0.05 and a power of 90% was assumed, with a total sample of 28 subjects estimated. Considering a 15% follow-up loss, we estimated a minimal sample size of 32 patients, with a minimal recruitment of 16 required for each of the intervention groups.

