## Abstract

Pain is an under-reported but prevalent symptom in Parkinson’s Disease (PD), impacting patients’ quality of life. Both pain and PD conditions cause cortical excitability reduction and non-invasive brain stimulation. Mental representation techniques are thought to be able to counteract it, also resulting effectively in chronic pain conditions. We aim to conduct two independent studies in order to evaluate the efficacy of transcranial direct current stimulation (tDCS) and mental representation protocol in the management of pain in PD patients during the ON state: (1) tDCS over the Primary Motor Cortex (M1); and (2) Action Observation (AO) and Motor Imagery (MI) training through a Brain-Computer Interface (BCI) using Virtual Reality (AO + MI-BCI). Both studies will include 32 subjects in a longitudinal prospective parallel randomized controlled trial design under different blinding conditions. The main outcomes will be score changes in King’s Parkinson’s Disease Pain Scale, Brief Pain Inventory, Temporal Summation, Conditioned Pain Modulation, and Pain Pressure Threshold. Assessment will be performed pre-intervention, post-intervention, and 15 days post-intervention, in both ON and OFF states.

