### 2.5. Data Analyses

The SPSS software package (version 25.00; SPSS inc., Chicago, IL, USA) will be used by a blinded statistician for statistical analysis of the data. Demographic and clinical variables will be presented as mean and standard deviation. A 95% confidence interval (CI) will be taken, considering statistically significant all those values that had a *p* < 0.05. Parametric statistical tests will be used for hypothesis testing (*n* > 30). To show differences in the main variables, an analysis of variance (ANOVA) 2 × 3 of repeated measurements will be carried out taking time and group as factors, being the groups active-tDCS (a-tDCS) vs. sham-tDCS (s-tDCS) in the tDCS-based study and AO+MI-BCI vs. AO-control AO+MI-based study, and the measurements times pre-treatment, post-treatment, and at 15 days post-treatment. If significant differences are found in any of the interactions, a post hoc analysis will be performed with Bonferroni correction. The effect sizes will be calculated by means of the d of Cohen, being classified as small (d between 0.20 and 0.49), medium (d between 0.50 and 0.79), or large (d greater than 0.80) following the method of Cohen.

For the rest of the psychological variables, a Pearson’s correlation with the physical variables will be carried out in order to find relationships between both. Low correlation will be taken as that with values between 0.2 and 0.39; the correlation will be considered moderate when the value goes from 0.40 to 0.79; and high when the value of the correlation is greater than 0.80.

For the analysis of neurophysiological variables rMT, MEP magnitudes will be determined by averaging peak-to peak amplitudes. The ratio of the rMT, MEP amplitude recorded at each post-intervention time-point relative to the baseline rMT will be calculated [(MEP amplitude at each stage–baseline MEP amplitude)/baseline MEP amplitude Å~100]. Statistical analyses will be performed on the calculated test-to baseline MEP ratios. For the CSP values the time will be measured manually in each trial and averaged and the ratio compared to baseline measurement will be also calculated.

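### KPDPS is primary only for sizing: five main outcomes are each tested at p < 0.05, and the active-versus-control superiority hypothesis is tied to no outcome or state

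*Protocol article*

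**What the plan says.** **Sizing.** Section 2.4.1 states "The primary outcome was chosen to be King’s Parkinson’s Disease Pain Scale". It uses f = 0.25, alpha 0.05 and 90% power for two groups and three times, and arrives at 28 patients, or 32 after 15% loss. Section 2.4.2 reuses these parameters for the second trial. No medication state is named.

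**Outcomes.** The abstract reads "The main outcomes will be score changes in King’s Parkinson’s Disease Pain Scale, Brief Pain Inventory, Temporal Summation, Conditioned Pain Modulation, and Pain Pressure Threshold". Section 2.3.1 places the same five under one heading with no order of importance. Some have more than one component:
- Section 2.3 says of KPDPS and two others: "CPM and TS will be also measured in OFF state, 30 min before medication intake".
- For PPT, "Two PPTs will be measured, one over the most painful area", the other being over the thumb.
- The BPI is described as "including 2 multi-item scales to measure the intensity of pain and its impact".

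**Analysis.** Section 2.5 runs a 2 × 3 repeated-measures ANOVA on the main variables, "considering statistically significant all those values that had a" p below 0.05. Bonferroni follows only as a post hoc step after a significant interaction. The separate ON/OFF analysis, with group, state and time factors, has the same post hoc correction and no other.

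**Hypothesis.** The Introduction says that each active technique will be superior to its control, without naming an outcome, a state or a test. Section 2.6 does tie a superiority decision to King's Pain Scale, but only for the later, conditional comparison of the two active protocols.

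**The concern.** The sizing section treats the trial as having one decisive test, while the outcome and analysis sections treat it as having at least five of equal rank, each at the full 5%. The Bonferroni step controls error among contrasts inside one ANOVA and does nothing across outcomes. Because the superiority hypothesis is not attached to any outcome, a significant TS or PPT result beside a null KPDPS result could be reported as confirming it, and nothing in the text would stand in the way. In a trial of 32 patients sized for a single test, such a finding would carry much weaker evidence than its nominal p-value suggests.

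**Working it through.** **1. The plan's own figure.** Inputs from section 2.4.1: f = 0.25, alpha = 0.05, k = 2 groups, m = 3 times, power 90%. The correlation between repeated measures (ρ) is not given. For the within-between interaction, λ = f²·N·m/(1 − ρ), with df (k − 1)(m − 1) = 2 and (N − k)(m − 1).

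- ρ = 0.5 (assumed), N = 28: λ = 0.0625 × 28 × 3 / 0.5 = 10.5, df 2 and 52, power 81.2%. Reaching 90% takes N = 36.
- ρ = 0.62 (assumed), N = 28: λ = 0.0625 × 28 × 3 / 0.38 = 13.8, power 90.9%.

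So 28 is reproduced only with an unstated ρ of about 0.62. That is a separate matter and not a proven error. What counts here is that the calculation spends the whole 5% on one test of one outcome.

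**2. Error rate with five main outcomes.** Take one group-by-time test per outcome at 0.05, with no true effect on any.

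- Independent tests: 1 − 0.95⁵ = 1 − 0.7738 = 22.6%.
- Correlated tests (simulation of equicorrelated two-sided z tests, 400,000 draws, as an approximation to the F tests):

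| Assumed correlation between tests | At least one false positive |
|---|---|
| 0 | 22.6% |
| 0.3 | 20.8% |
| 0.5 | 18.4% |
| 0.7 | 14.8% |

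The correlations are assumptions. Some positive correlation is likely, because thumb PPT sets the TS intensity and the CPM test stimulus is also a thumb PPT. The rate applies to each trial separately.

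**3. What each remedy would cost in sample size.**

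- One confirmatory outcome: alpha stays 0.05, so multiplicity does not change N.
- Five co-equal outcomes with Bonferroni: alpha = 0.05/5 = 0.01. For 90% power N = 50 at ρ = 0.5, or 38 at ρ = 0.62. With 28 completers, power is 59% or 75% respectively.

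**The case against.** The strongest reply is that one primary outcome is already named, that the only explicit superiority rule (section 2.6) uses the same scale, and that no sentence says superiority will be declared if any main outcome is significant. A reader might infer such an any-outcome rule. The documents do not state it: the inference comes from a hypothesis with no outcome attached and a threshold applied to everything. What stands is narrower. The document names KPDPS as primary only to justify N, and never makes it decisive for active versus control.

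A reader might also count ten or eleven tests, adding OFF-state KPDPS, CPM and TS, the second PPT site, the second BPI scale and residual CPM, and arrive at 40% or more under independence (1 − 0.95¹⁰ = 40.1%). The documents do not support that count. OFF-state data go into an ANOVA with group, state and time factors, not a second set of 2 × 3 ANOVAs, and no separate tests are specified for the BPI scales or for residual CPM. Such tests could raise the rate, but their number is not stated, so the five headline outcomes should carry the point.

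It can also be said that endpoint hierarchy is often left to an analysis plan that is not shown. Here, though, the article itself fixes the five main outcomes, the common threshold and a correction confined to post hoc tests. An analysis plan could repair this only by departing from the published text.

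**Conclusion.** The point holds in this limited form: the single-outcome sizing conflicts with five unranked main outcomes each tested at 5%, and the active-versus-control hypothesis is tied to neither an outcome nor a state. The chance of at least one false positive per trial is about 15% to 23%, three to four and a half times the nominal 5%. This assumes five tests, no true effects and correlations between 0.7 and 0. The conclusion does not extend to the comparison of the two active protocols in section 2.6, which is tied to KPDPS.

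**What to change.** State in the abstract, section 2.3.1 and section 2.5 that the sole confirmatory test in each trial is the planned group-by-time interaction for KPDPS total score in the ON state, two-sided at 5%, and attach the Introduction's superiority hypothesis to it. ON is the state named in the abstract's aim and the one in which section 2.2 places the treatment sessions. Relabel BPI, PPT, TS, CPM and all OFF-state measures as secondary, report them with confidence intervals, and apply Holm's adjustment if any claim is to be made from them.

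The planned test should stay. Replacing it with a contrast at a single visit would change the analysis on which the trial was sized, and is not needed to cure this defect.

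The cost is wording in these places and a check that the registry entries, which are not visible here, agree. Multiplicity does not require a larger sample. The real concession is that an isolated effect on BPI, PPT, TS, CPM or an OFF-state measure can no longer support the superiority claim.
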